### Randomization and blinding

After completing the baseline assessment, the participants will be randomized into three intervention groups; twice-weekly KBA, thrice-weekly KBA, and conventional physiotherapy (control) in the ratio of 1:1:1. The randomization will be performed using an online randomization generator (http://www.randomization.com) by utilizing block randomization with a block size of 3 and 6. A third party not  involved in the study will perform the randomization process. Allocation of participants will be concealed using consecutive numbered, sealed, and opaque envelopes. The outcome assessors (physiotherapists) will be blinded to the group allocation and will not be involved in administering the interventions. The participants will be told they are in a “twice weekly KBA” or “thrice-weekly KBA” or “conventional physiotherapy,” but the type of intervention will not be specified. Conversely, due to the nature of the interventions, it will be difficult to blind the physiotherapists providing the treatments. Unbinding conditions will be only permissible when there is a medical emergency.

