### Knee stability

Participants’ subjective reports of knee stability will be measured with the Knee Outcome Survey-Activities of Daily Living Scale (KOS-ADLS). It is a 14-item questionnaire that assesses symptom-related and specific functional limitations [55]. Six items assess knee symptoms (pain, stiffness, swelling, instability, weakness, and limping), and eight items assess functional limitations (walking, stairs ascent/descent, standing, kneeling, squatting, sitting, and rising from a sitting position) experienced in the last 1 to 2 days during the performance of daily activities. Each item is scored on a 6-point Likert scale (0–5 points) [56]. The score is transformed to a 0–100 point scale with the highest score indicating the absence of symptoms and functional limitations [55]. For the purpose of this study, only the item pertaining to knee instability symptoms will be evaluated. The KOS-ADLS has been shown to have excellent internal consistency (0.92–0.93), test-retest reliability (intraclass correlation coefficient [ICC] = 0.97), and adequate construct validity [55].

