### Statistical analysis

An independent statistician who will be blinded to the study procedures will conduct all statistical analyses. The normality test of the data will be verified with the Shapiro–Wilk test and visual inspection of distribution plots. To account for potential missing data in datasets, per-protocol (PP) and intention-to-treat (ITT) approaches will be considered for the data analysis. For the PP approach, only participants who completed all treatment sessions will be included in the analysis. For the ITT approach, multivariate imputation by chained equations will be employed [68]. Descriptive statistics of mean and standard deviation will be used to summarize all continuous variables while frequency and percentages will be used to summarize all categorical variables. Mixed between-within subject ANOVA will be used to assess interaction effect (group x time), main effects for time, and between-subjects effect if the data is normally distributed. However, Friedman’s ANOVA and Kruskal–Wallis test will be used to analyze within-group change and between-group difference, respectively, if the data is not normally distributed. Post hoc analysis using Bonferroni correction will be conducted for any significant between-group difference observed. Effect size will be also computed to determine the magnitude of change in outcomes. All data will be analyzed using SPSS version 23 (IBM Co., Armonk, NY, USA) at an alpha level of 0.05.

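### A normality check with no stated decision rule chooses each outcome's analysis, and the fallback as written has no group-by-time test, does not combine visits and does not adjust for baseline

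*Protocol article*

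**What the plan says.** All of the following is in the protocol article.

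- **Check** (Statistical analysis): "The normality test of the data will be verified with the Shapiro–Wilk test and visual inspection of distribution plots". The text does not say whether this is applied to values by arm and visit, values pooled by visit, change scores or residuals. It gives no rule for combining the test with the plots.
- **Branch if normal** (same section): "Mixed between-within subject ANOVA will be used to assess interaction effect (group x time), main effects for time, and between-subjects effect".
- **Branch if not normal** (same section): Friedman's ANOVA and the Kruskal–Wallis "test will be used to analyze within-group change and between-group difference, respectively, if the data is not normally distributed". No interaction test is named here, and the text does not say whether Kruskal–Wallis is applied to follow-up values or to change scores.
- **Follow-on** (same section): "Post hoc analysis using Bonferroni correction will be conducted for any significant between-group difference observed". An effect size is also promised, without a definition. The section closes by setting all analyses "at an alpha level of 0.05".
- **Design**: three arms (Randomization and blinding), with every outcome measured at five time points (Outcome assessments and follow-ups).
- **Knee stability** is taken from KOS-ADLS, but "only the item pertaining to knee instability symptoms will be evaluated". Each item is scored 0 to 5.

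**The concern.** The trial asks which KBA frequency is superior, which is a between-arm question followed over time. The mixed ANOVA addresses it through group by time. The fallback splits it in two: Friedman compares visits inside one arm and does not compare arms, and Kruskal–Wallis compares arms without a covariate and without combining visits. These are not two versions of one analysis. Two outcomes in the same trial could be reported on different questions because one passed a preliminary test and the other did not.

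The trigger is also loose. The mixed ANOVA relies on approximately normal residuals, whereas the text speaks only of the data. With no unit and no decision rule, the analysis of the primary outcome can be settled after the data have been seen. Finally, separate within-arm p-values beside a between-arm test make it easy to report that one arm improved and another did not, which is not a comparison of arms.

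**Working it through.** The plan gives no figure for how often the switch would operate, so there is none of its own to reproduce on this point.

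**1. False alarms of Shapiro–Wilk on exactly normal data**

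Inputs: 3 arms and 5 assessments, so 3 × 5 = 15 arm-by-visit cells per outcome, and 40 per arm (Sample size estimation). Assumptions: Shapiro–Wilk is run at 0.05, any rejection triggers the switch, and the within-person correlation (not given) lies between 0 and 0.9. With k independent tests the rate is 1 − 0.95^k.

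| How the check is applied | k | Formula | Simulated |
|---|---|---|---|
| One pooled or residual test | 1 | 5% | about 5% |
| Three arms at one visit | 3 | 1 − 0.95³ = 14.3% | 13–15% |
| Any of five visits, arms pooled | 5 | 1 − 0.95⁵ = 22.6% | about 16–24% |
| Any of 15 cells | 15 | 1 − 0.95¹⁵ = 53.7% | about 40–54% |

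The lower ends of the last two rows belong to the highest correlation.

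**2. The knee-instability item**

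A six-level item was simulated as rounded normal scores (SD 0.8 to 1.6, assumed). Shapiro–Wilk rejected in 100% of samples at 40 per arm, in 88–100% at 34 per arm and in 100% at 120 pooled. Five visits give repeated chances to reject, so the fallback is close to certain for this outcome.

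**3. What the fallback costs in power at one follow-up visit**

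Assumed effect: arm means 0, 0.3 and 0.6 SD, with 32 per arm (40 less 20%). Cohen's f is the SD of the arm means over the within-arm SD: √[((−0.3)² + 0² + 0.3²)/3] = √0.06 = 0.245.

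| Method (normal data, simulated) | Correlation 0.5 | Correlation 0.7 |
|---|---|---|
| Kruskal–Wallis on follow-up values | 53% | 53% |
| ANOVA on follow-up values | 55% | 55% |
| Kruskal–Wallis on change scores | 53% | 75% |
| ANOVA on change (pre/post group by time) | 55% | 78% |
| ANCOVA adjusted for baseline | 68% | 84% |

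The entries carry simulation error of a point or two. On the same scores, ranks cost about 2 to 3 points. The rest of the distance to ANCOVA comes from how baseline is used.

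**4. The same comparison at the planned effect**

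The Sample size estimation section gives 0.185 and 0.47. If 0.185 is read as eta-squared, f = √(0.185/0.815) = 0.476, close to 0.47, so 0.47 is read here as f. At f = 0.47 every method has at least 98% power, with 32 or 34 per arm.

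**The case against.** Four points can fairly be made for the plan.

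- **The switch need not fire often.** A reader might infer that it would regularly fire on normal data. The article does not support that: the unit tested is not stated, a single residual test gives 5%, and plots share the decision. The unit may be set out in an analysis plan that is not shown. This stands, so only a range can be given. It does not rescue the branch structure, which the article itself fixes.
- **Baseline is not excluded.** A reader might infer that the fallback cannot use baseline. Kruskal–Wallis on change scores would use it and would give a two-time-point form of group by time, and Friedman across visits includes the baseline visit. This stands as a possibility. The text does not provide for change scores, and they would still neither combine follow-up visits nor match ANCOVA.
- **Friedman is not offered as evidence of a treatment effect.** The text assigns it to within-group change only. This stands, and the risk lies in how the results are read.
- **The ANCOVA comparison overstates the cost of switching.** ANCOVA is in neither branch. Against the mixed ANOVA's own pre/post contrast, the loss is about 2 points at correlation 0.5 (55% to 53%). At 0.7 it is about 25 (78% to 53%), most of which change scores would recover. This stands, and the ANCOVA figures belong to the case for the replacement model.

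A rank test is also a defensible between-arm analysis for one ordinal item. For that outcome the problem is that a normality test reaches an answer that could simply have been pre-specified.

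**Conclusion.** The concern holds for the structure of the analysis. A data-driven check with no stated unit or rule selects between two analyses that answer different questions, for every outcome including the primary one. One named secondary outcome will almost certainly take the branch without a group-by-time test.

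Its size depends on assumptions. The false-alarm range of 5% to about 54% rests on a 0.05 level, any rejection triggering the switch, and no tempering by the plots. The power figures rest on an assumed effect about half the planned one (0.245 against 0.47) and assumed correlations of 0.5 and 0.7. A reader might infer that the fallback leaves the trial underpowered. On the plan's own effect size it does not, and the loss matters only for smaller differences between arms. The change should be made, but nothing here shows that the primary result would be wrong.

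**What to change.** Delete the switch in the Statistical analysis section.

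- **IKHOAM, VAS-pain, absolute angular error and OAKHQOL scores:** pre-specify one model, for example a linear mixed model with baseline value, group, visit and group by visit, used whatever the Shapiro–Wilk result. Judge assumptions on residuals. Keep rank-based, bootstrap or robust-variance results as sensitivity analyses.
- **Knee-instability item:** pre-specify one between-arm analysis suited to an ordinal score, for example a proportional-odds model adjusted for baseline.
- **Friedman tests within arms:** if kept, label them descriptive.

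The cost is analysis wording and a small amount of extra analysis. All the data needed are already collected at the five planned assessments, so no participant or visit is added.

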It is conceivable that the small to moderate effect sizes detected in exercise-based RCTs on knee OA may be due to insufficient dose used [20]. It has recently been suggested that evidence-based proprioceptive training should consider training frequency of at least three times per week, for 30 to 40 min per session to achieve the highest effectiveness [34]. The frequency and number of sets to be performed therefore should be taken into consideration when designing proprioceptive-based training programs for knee OA individuals as these exercise programs may appear challenging especially among older individuals. Thus, this study will be conducted to determine which frequency of structured KBA exercise training (i.e., twice-weekly or thrice-weekly) will produce superior therapeutic outcomes in adults with knee OA. The primary outcome will be physical function whereas secondary outcomes will be pain intensity, knee stability, proprioception, and quality of life.

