### Sample size estimation

Based on the results of our pilot study (unpublished data), using the effect size of 0.185 for between-group difference in the primary outcome (physical function measured by IKHOAM), a priori sample size was calculated assuming a statistical power of 90%, an alpha of 5% (two-tailed), and an effect size of 0.47. The calculations suggested a sample size of 102 would be needed. However, while anticipating a 20% attrition rate (*n* = 20), a total sample size of 120 will be needed with 40 participants per group. The calculations were performed with the G-power 3.1.9.2 software (University of Dusseldorf, Dusseldorf, Germany) [67].

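### The contrast between thrice- and twice-weekly KBA, which is the main question, is neither planned nor tied to the stated power, and is reached only post hoc with a Bonferroni step that three arms do not need

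*Protocol article*

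**What the plan says.** The Background section of the protocol article gives the purpose as "to determine which frequency of structured KBA exercise training (i.e., twice-weekly or thrice-weekly) will produce superior therapeutic outcomes in adults with knee OA". The Discussion adds the effectiveness of KBA as something the trial may inform, so the comparisons with conventional physiotherapy also matter.

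The Sample size estimation section starts from a pilot result, "using the effect size of 0.185 for between-group difference in the primary outcome (physical function measured by IKHOAM", and continues: "a priori sample size was calculated assuming a statistical power of 90%, an alpha of 5% (two-tailed), and an effect size of 0.47". The result is 102. Allowing for 20% attrition, the article concludes that "a total sample size of 120 will be needed with 40 participants per group". It names no test, no effect-size metric and no pair of arms.

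The Statistical analysis section plans a three-group mixed ANOVA, or Kruskal–Wallis and Friedman tests if the data are not normal. On pairs of arms it says only: "Post hoc analysis using Bonferroni correction will be conducted for any significant between-group difference observed". It does not single out thrice versus twice weekly, and it does not give the number of pairs corrected for.

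**The concern.** The aim is a comparison of two arms, while the power statement and the testing rule both concern a difference somewhere among three. Both KBA arms also receive the whole conventional programme (Interventions section), so they differ from each other only in the number of KBA sessions. A gap between them smaller than the gap from control is plausible. The trial could then show a clear overall result, driven by KBA against control, and have modest power on frequency.

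The Bonferroni step lowers that power further. If the frequency contrast comes out non-significant, a reader who has seen the 90% may take it as evidence that the third weekly session adds nothing. The article does not plan such a conclusion, but nothing in its stated analysis guards against it.

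**Working it through.** **Inputs from the protocol article.** Effect sizes 0.185 and 0.47, power 90%, two-tailed alpha 0.05, calculated N = 102, enrolled N = 120 (40 per arm), attrition 20% (all from Sample size estimation). Completers: 120 × 0.8 = 96, or 32 per arm.

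**Assumptions not in the article.** Three pairs under Bonferroni, so alpha = 0.05/3 = 0.0167; a comparison at a single time point; the metric of 0.47 and the spacing of the arm means, both varied below.

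**1. What 0.47 is likely to be.** Read 0.185 as eta squared: f = √(0.185/(1 − 0.185)) = √(0.185/0.815) = 0.476. This nearly equals 0.47, so Cohen's f is the most plausible metric.

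**2. The plan's own figure.** For a one-way three-group F test with λ = f²N and df 2 and N − 3, at f = 0.47:

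| N | Power |
|---|---|
| 61 | 90.3% |
| 63 (equal arms) | 91.3% |
| 96 | 98.7% |
| 102 | 99.1% |
| 120 | 99.7% |

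So 102 is not the N for 90% omnibus power at f = 0.47; it would match f of about 0.358. A two-sample t test at d = 0.47 needs 97 per arm, which does not give 102 either. Between-subject, within-subject and interaction tests over two to five time points did not yield it. The stated figure is not reproduced.

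**3. What f = 0.47 says about the KBA gap (in SD).**
- Both KBA arms equal and both above control: each exceeds control by 0.47 × √4.5 = 1.00, and the KBA gap is 0.
- Equally spaced arms: range 0.47 × √6 = 1.15, adjacent gap 1.15/2 = 0.576.
- Twice weekly equal to control, thrice weekly alone better: gap 1.00.
- Largest gap compatible with this f: 1.15.

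**4. Power for thrice versus twice weekly.** Noncentral t with noncentrality d√(n/2) and pooled error df 3n − 3:

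| Gap d | n per arm | Bonferroni (0.0167) | Alpha 0.05 |
|---|---|---|---|
| 0.47 (if 0.47 is the pairwise d) | 32 | 29% | 46% |
| 0.47 | 40 | 38% | 55% |
| 0.576 (equally spaced, f = 0.47) | 32 | 45% | 62% |
| 0.576 | 40 | 56% | 72% |
| 1.00 | 32 | 94% | 98% |
| 1.15 | 32 | 98% | 99.5% |

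Simulating the F test followed by the pairwise test gives the same values for the equally spaced case at 32 per arm (44.9% and 62.5%).

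**5. Gap detectable with 90% power at 32 per arm.** About 0.94 SD at 0.0167 and about 0.82 SD at 0.05.

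**6. Is Bonferroni needed after the gate?** With exactly three arms, one outcome and one time point, a significant three-group F test followed by unadjusted pairwise tests is a closed procedure. In simulation its family-wise error was 0.049 to 0.050, both with all arms equal and with one arm different. With both KBA arms equal and control 1 SD lower, it falsely declared a frequency difference in 5.0% of runs, and the planned rule did so in 1.9%.

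**The case against.** The strongest reply has four parts.

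- **Tempting over-reading of the 90%.** A reader might infer that the 90% belongs to the omnibus test. The article never says so, and its inputs contradict it: that test has about 99% power at 102. This stands, and a correction sentence to that effect would be wrong.
- **Tempting over-reading of the 45%.** A reader might take 45% as the trial's power on its main question. It is one scenario. At f = 0.47 the gap may be anywhere from 0 to 1.15 SD, and Bonferroni power is 94% if only the thrice-weekly arm works. This also stands, so only a range with its assumptions can be given.
- **Bonferroni is valid.** True: it is conservative, not wrong. The closed-test argument covers one outcome at one time point. A significant group-by-time interaction over five assessments does not by itself license unadjusted pairwise tests at a chosen visit.
- **Several aims, and detail left to other documents.** The Discussion also names KBA effectiveness, and key contrasts and intervals are often set out in a fuller protocol or analysis plan. The first part is fair, and the three-pair procedure serves that aim too. The second does not remove the point, because the article itself states a power basis and a pairwise rule, and neither is matched to its stated purpose.

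**Conclusion.** The point holds in limited form. The frequency contrast is not planned as such, and the 90% cannot be applied to it, because an overall effect size leaves the gap between the KBA arms open. At 32 completers per arm, power is about 45% with Bonferroni and 62% without if 0.47 is Cohen's f and the arms are equally spaced, and 29% and 46% if 0.47 is the pairwise difference. Under Bonferroni it reaches 90% only for a gap of about 0.94 SD or more. These figures rest on three pairs, a single time point and the attrition stated in the article.

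The extra Bonferroni step costs about 17 percentage points in the equally spaced case (62% against 45%) and buys no needed protection for three arms on one outcome at one time point. The documents do not support saying that the 90% is an omnibus figure, or that the trial simply has 45% power.

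**What to change.** **Statistical analysis section.** Name thrice minus twice weekly on IKHOAM, at one stated primary time point, as the planned key contrast. At that time point run the three-group test and, if it is significant, test the three pairs each at two-sided 0.05 in place of Bonferroni. Report the thrice–twice difference with its 95% CI whatever the test result, and say that a non-significant difference will not be read as equal effect.

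**Sample size estimation section.** State which test and which effect-size metric produced 102, and correct the figure if it does not reproduce. Do not write that 90% refers to the omnibus test. Add the detectable thrice–twice difference: about 0.82 SD for 90% power at 32 per arm and alpha 0.05.

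**Cost.** Wording only, to be settled before any analysis, with no added participants. The less favourable power for the key contrast becomes visible, and the unadjusted intervals are not simultaneous. The change does not restore 90% power: at alpha 0.05 that would take about 64 completers per arm for a gap of 0.576 SD, or 97 for 0.47 SD.

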### Data management

After baseline assessment, all participants will be recognized only by their initials and numbers. Data will be stored using paper files, computer hard drive, and electronically to have a backup copy. All data values will be double-checked by assessors to check for errors and missing values before analysis.

### Dissemination

The results of this study will be submitted for publication to an international peer-reviewed journal irrespective of whether the results are positive, negative, or inconclusive.

## Discussion

There is evidence to suggest proprioceptive deficits in individuals with knee OA and that neuromuscular training programs targeting to improve proprioception are beneficial among these individuals [29–34]. The effectiveness of KBA as a proprioceptive training program in individuals with knee OA has been recently tested in clinical trials [36, 44–48], however, clinicians need to know the ideal dosage of KBA associated with the highest effectiveness as results of these previous trials were mixed. The present study will be aiming to determine the effects of a structured KBA exercise training program with different frequencies of treatment sessions (i.e., twice-weekly or thrice-weekly) on physical function, pain intensity, knee stability, proprioception, and quality of life in adults with knee OA. The outcomes will be evaluated at 8 weeks, 3 months, 4 months, and 6 months after randomization. We hope to follow-up the patients for a year if the 6-month follow-up results suggest this would be useful.

The findings of this study may provide evidence on the effectiveness of the KBA exercise training and the ideal number of sessions needed to achieve the highest effectiveness, which may guide clinical practice and minimize waste of time and resources.

Potential factors that could account for the limitations of the present study may include the lack of blinding of the treating therapists due to the nature of the interventions. Furthermore, because the present study is a multi-center trial employing the services of different treatment therapists with different skills and expertise, we cannot rule out the possibility of differential treatment. However, the assessor blind, three-arm RCT design with concealed allocation can be considered as the strengths of our study.

